##### Cardiorespiratory Fitness

This will be measured by a 2-minute step test. The evaluator will count the number of full steps completed by the participant in 2 minutes. A full step is defined as a step performed while raising the knee up to a height corresponding to the midpoint between the patella and the iliac crest [54].

#### Secondary Outcomes

##### Upper Limb Strength

This will be estimated using the grip strength test, which uses a previously calibrated Baseline hydraulic dynamometer. This evaluation will be carried out with the older adult seated on a chair with a backrest, shoulders adducted, elbow flexed at 90°, forearm, and wrist in a neutral position. The evaluated arm should not rest on any surface, and the dynamometer should be used vertically. Older adults will be asked to perform a maximum grip force with their dominant hand for 3 seconds, resting for 1 minute between each repetition, making 2 attempts. The highest grip value of the repetitions will be used. This protocol is described in Encuesta nacional de salud 2016 to 2017.

##### Dynamic Balance

This will be measured with the Timed Up and Go test. The older adult will be seated on a chair without armrests, with the back against the backrest and feet touching the ground. The older adult will be asked to stand up and walk as usual to a cone located 3 m away, turn around, and return to sit down. This test controls the time it takes to complete the circuit, starting from the moment the older adult lifts their back from the chair and ending when returning to the start position. The scale is normal ≤10 seconds, with a slight risk of falling at 11 to 20 seconds and a high risk of >20 seconds [55].

##### Static Balance

This will be measured using the single-leg stance test. The participants will be asked to cross their arms over their chest, rest their hands on their shoulders, and triple-flex one leg at 90°, staying as long as possible on 1 foot (maximum of 30 s). The test will be repeated 3 times, and the best time obtained will be considered for the study. According to national studies, it is assumed that an older adult has a high risk of falling due to not being able to maintain this position for ≥5 seconds [55].

##### Quality of Life

This will use the 36-item Short Form Health Survey (SF-36) questionnaire [56,57] in its Spanish version [58]. The SF-36 is a self-report instrument that contains 36 questions from 8 dimensions related to people’s health: physical function, physical role, bodily pain, vitality, social function, emotional role, mental health, and general health [59]. The score obtained corresponds to values on a scale of 0 to 100, where higher scores indicate better health [59]. The SF-36 is adapted and validated in Chilean older adults, presenting adequate indicators of general Cronbach α internal consistency of .88 [60].

##### Functional Status

It will be measured by using the Functional Independence Measure. It is composed of 18 items, with a total score ranging from 18 to 126, and it allows quantifying the demand for help from third parties that a person needs to perform their daily life activities. The evaluated items include self-care activities, sphincter control, locomotion, mobility or transfer, and social cognition. For each evaluated activity, the score ranges from 1 (totally dependent) to 7 (totally independent) [61]. The Functional Independence Measure is one of the most widely used instruments to carry out functional evaluation in rehabilitation, validated for the older adults [62], presents clinical validity, agreement between evaluators, test-retest, and intraobserver reliability, and has been widely used in Chile [63].

##### Number of Daily Steps

Each participant will wear a digital pedometer for 7 consecutive days. The total number of steps recorded during this period will be summed and divided by the number of days the pedometer was worn to calculate the average daily step count. Each participant will receive instructions and an illustrative guide with specific care of the equipment. We will use the classification proposed by Tudor-Locke and Bassett, which indicates that the number of steps represents the level of physical activity: <2500 steps/day (basal activity); 2500 to 4999 steps/day (limited activity); 5000 to 7499 steps/day (low activity); 7500 to 9999 steps/day (mildly active); 10,000 to 12,499 steps/day (active); >12,500 steps/day (highly active) [64].

#### Sociodemographic Background

The sociodemographic characteristics of the participants will be recorded, including age, gender (male or female), geographical origin (rural or urban), educational level (basic education: <8 years, middle education: 8-12 years, and higher education: >12 years), and the presence of comorbidities such as diabetes mellitus, hypertension, and dyslipidemia. Nutritional status will be classified based on BMI, which is obtained by dividing body weight by bipedal height squared (weight/height^2^), with cutoff points considered, low weight: <22.9 kg/m^2^, normal weight: 23.0 to 27.9 kg/m^2^, overweight: 28.0 to 31.9 kg/m^2^, and obesity: ≥32 kg/m^2^ [65]. The questions and the classification indicated in the National Health Survey 2016 to 2017 will be used.

### Ethical Considerations

The study was conducted in accordance with the Declaration of Helsinki [66] and approved by the University Santo Tomas Ethics Committee (CEC Accredited Res. No. 01-MZS, approved on May 24, 2024). Informed consent will be obtained from all participants involved in the study.

### Statistical Analysis

Missing data will be handled by intention-to-treat analysis (multiple imputation method) [67]. The description will be made as measures of central tendency and dispersion (continuous variables) and as percentages (categorical variables). Using the Shapiro-Wilk test, the normality of the data will be verified, and a two-step approach for transforming will be applied to the nonnormal variables [68]. Homoscedasticity will be analyzed using Levene test. A 2-way repeated measures ANOVA will be used to determine the effects of interventions. The effects of the model are the group (experimental group vs control group), the time points (before and after test), and their interaction over time (time × group). The Bonferroni post hoc test will be applied to identify statistically significant comparisons. The *t* test effect size will be determined using Cohen *d* (<0.2 insignificant; ≥0.2 and ≤0.49 small; ≥0.5 and ≤0.79 moderate; ≥0.8 large) [69]. All analyses will be performed using SPSS (version 26; IBM Corp), with a significance level of *P*<.05, and GraphPad Prism (version 8).

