### Objectives

In this context, this study aims to analyze whether the effectiveness of an STR program is better than a face-to-face physical therapy (FPT) program in the primary outcomes (lower body strength and cardiorespiratory fitness) and secondary outcomes (upper limb strength, dynamic balance, static balance, number of steps, functional status, and quality of life) in older adults who are frail. We hypothesize that (1) both STR and FPT programs improve primary (lower body strength and cardiorespiratory fitness) and secondary outcomes (upper limb strength, dynamic balance, static balance, number of steps, functional status, and quality of life) in older adults who are frail and (2) STR produces equal or greater improvements compared to face-to-face programs in these outcomes.

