### Power Calculation

The sample size was calculated a priori using G*Power 3.1.9.7. A total of 52 participants in total are required (26 in each group), considering Cronbach α=.05, 1-β=.8, and effect size=0.8 (lower limb strength based on the results of a previous study) [19]. Considering the possibility of abandonment, 6 participants were added (N=58; n=29 in each group; Figure 1 [42]).

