### Randomization

The sample will be selected by quota until a size of 58 participants is reached. The selection will be random among those who meet the inclusion and exclusion criteria. Participants will be randomized by research staff using a computer-generated sequence and concealed allocation to one of the following two groups: (1) the STR group, which will receive STR, or (2) the FPT group, which will receive FPT. A simple randomization computational sequence stratified by gender, age, and frailty will be used to obtain a balance between men and women, age ranges, and severity of frailty in both groups. The randomization sequence will be concealed using sequentially numbered, opaque, sealed envelopes to ensure allocation concealment (Figure 1).

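### The two-time-point repeated measures ANOVA compares the arms through change scores, which is valid but less precise than baseline adjustment; it omits the stratification factors, and hypothesis 1 rests on before/after change alone

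*Protocol article*

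**What the plan says.** Statistical Analysis: "A 2-way repeated measures ANOVA will be used to determine the effects of interventions". The section then lists the model's effects: group, time (before and after) and time × group. No baseline covariate and no stratification factor appears. It continues: "The Bonferroni post hoc test will be applied to identify statistically significant comparisons", without saying which comparisons are meant. None of the three effects is named as the one that answers the trial's question.

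Randomization: the allocation sequence is "stratified by gender, age, and frailty", with the stated purpose of balancing the two groups on these factors.

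Objectives: the aim is between-arm, namely whether STR does better than FPT. Hypothesis 1 is of another kind: "both STR and FPT programs improve primary (lower body strength and cardiorespiratory fitness) and secondary outcomes". Hypothesis 2 is that STR does at least as well as the face-to-face program.

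Power Calculation: "A total of 52 participants in total are required (26 in each group"), "considering Cronbach α=.05, 1-β=.8, and effect size=0.8". With the dropout allowance, "6 participants were added (N=58; n=29 in each group").

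**The concern.** Three features of the published model deserve attention.

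- **Precision.** With two time points, the interaction test uses the baseline only by subtracting it. Regressing the post value on baseline uses the same data with less residual noise, which matters in a trial of 58 people.
- **Which effect decides.** Group, time and interaction answer different questions. Time compares no arms. Group averages the pre-intervention value, where no treatment effect can exist, with the post value, and so shows only half the effect. Only the interaction directly addresses the stated aim, and the text does not say so.
- **Hypothesis 1.** Both arms exercise. The claim that both programs improve outcomes can be tested only by before/after change, either pooled (the time effect) or within each arm. Such change mixes any treatment effect with practice on the tests, the passage of time, the education sessions given to everyone, and regression to the mean.

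At stake are power that could be had from data already collected, and the risk that effectiveness is claimed from before/after P values.

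**Working it through.** **Inputs.** From Power Calculation: 26 evaluable per arm, alpha 0.05, power 0.80, effect size 0.8. From Statistical Analysis: the three model terms. From Outcome Measures: one assessment before and one after. Assumptions, because the protocol does not give them: two-sided testing; equal pre and post SDs, set to 1; rho over a range; d as the difference in post values in SD units. Besides the planned 0.8, d = 0.5 is used, the lower edge of what the protocol's own effect-size bands call moderate.

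**The plan's figure.** A two-sided two-sample t test with d = 0.8 has power 0.7915 at 25 per arm and 0.8075 at 26, so 52 in total reproduces. Adding 6 gives 58, an allowance of 6/58 = 10.3%.

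**Interaction equals change score.** In a simulated data set of this design, the interaction F was 15.478 and the squared t on change scores was 15.478.

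**Variances per participant.**
- Change score: 2(1 − rho)
- Baseline-adjusted: 1 − rho²
- Ratio: (1 − rho²) / [2(1 − rho)] = (1 + rho)/2, below 1 whenever rho < 1

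**Power.** The noncentrality is d / [SD × √(2/26)], with √(2/26) = 0.2774, on 50 df for change scores and 49 df for the adjusted test. For d = 0.5 and rho 0.5, the change-score SD is √1 = 1, the noncentrality 1.80 and the power 0.42. The adjusted SD is √0.75 = 0.866, the noncentrality 2.08 and the power 0.53.

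| rho | variance ratio | d = 0.5: change | d = 0.5: adjusted | d = 0.8: change | d = 0.8: adjusted |
|---|---|---|---|---|---|
| 0.3 | 0.65 | 0.32 | 0.46 | 0.67 | 0.84 |
| 0.5 | 0.75 | 0.42 | 0.53 | 0.81 | 0.90 |
| 0.7 | 0.85 | 0.63 | 0.70 | 0.955 | 0.977 |
| 0.8 | 0.90 | 0.80 | 0.84 | 0.994 | 0.997 |
| 0.9 | 0.95 | 0.977 | 0.982 | about 1 | about 1 |

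Simulation at d = 0.8 agreed: 68.0% against 83.5% at rho 0.3, 80.5% against 89.6% at rho 0.5, and 95.1% against 97.3% at rho 0.7. Type I error was 4.3% to 5.3% for both tests.

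**Adding the stratification factors.** The table is for adjustment on baseline alone. Simulations that added three binary factors unrelated to outcome gave variance ratios against the change score of about 0.83, 0.90 to 0.94, 0.98 and 1.03 at rho 0.5, 0.7, 0.8 and 0.9. Against baseline-only adjustment this costs 1 to 3 points of power. With moderately prognostic factors the cost disappears: at rho 0.5 and d = 0.8, power was 91.6%, against 80.2% for the change score.

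**Why the deciding effect should be named.** The group main effect has mean d/2 and SD √[(1 + rho)/2]. At d = 0.8 and rho 0.7 the noncentrality is 0.4 / (0.922 × 0.2774) = 1.56 and the power 0.34, against 0.955 for the interaction.

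**The case against.** The strongest reply is that the planned test is sound. Under randomisation the interaction is unbiased with correct type I error, and leaving out the stratification factors does not inflate that error. Preferring a more efficient valid test is an improvement, not the repair of a mistake. This stands, and it limits the weight of the point.

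The size of the gain also depends on a correlation that the protocol does not give, and the tabulated gains do not carry over unchanged to a model with the stratification terms. Age ranges and frailty levels are not defined in the Randomization section, so even the number of terms is unknown. This stands too; the gain cannot be called free.

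It can be added that covariates and the deciding contrast are often left to an analysis plan that is not shown. That is weaker here, because the article writes out the model's effects in full.

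Three stronger readings are tempting and are not supported:

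- A reader might infer that the trial will be judged on the group main effect, with power near 0.34. Nothing in the text says so, and the interaction is listed. The figure only illustrates why the deciding effect should be named.
- A reader might infer that the Bonferroni comparisons are within-arm tests. A 2×2 design has four simple effects, two within arms and two between, and the text does not say which will be run.
- A reader might attach a rate of false improvement to regression to the mean. Participants are selected on the modified Fried phenotype, not on a threshold of a primary outcome test, so the protocol supports no such number.

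**Conclusion.** The published analysis is valid but not the best use of the data. Baseline adjustment gives (1+rho)/2 of the change-score variance, assuming equal pre and post SDs. At 26 per arm and d = 0.5 that is a gain of about 11 points of power at rho 0.5 and 7 points at rho 0.7, shrinking above 0.8. If the planned 0.8 is a difference in post values, the interaction falls below the intended 80% power when rho is under 0.5, while the adjusted test stays at about 80% or more. If it is already on the change scale, the planned power holds whatever rho is; the protocol does not say which applies.

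Separately, and without any numerical assumption, before/after change in a trial with no unexercised arm cannot support hypothesis 1 as a claim of effectiveness. The omission of the stratification factors is a matter of precision and of matching analysis to design, not of bias. This is a recommended change rather than an essential correction.

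**What to change.** Replace the ANOVA in Statistical Analysis, for each outcome, by a linear model of the post value on arm, baseline value, and gender, age and frailty severity coded as at randomisation. Name the arm coefficient with its 95% CI as the single deciding effect, pooled over the planned imputations by Rubin's rules. Report within-arm changes as means with CIs, without significance tests, and reword hypothesis 1 so that no effectiveness claim rests on them. Settle this before the analyst sees data by arm.

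Cost: a wording change. It needs no further participants or measurements, and the same software serves. It uses a few degrees of freedom. If the stratification terms turn out not to be prognostic, expect to lose about 1 to 3 points of power relative to baseline-only adjustment; at rho of about 0.85 or more this can cancel the gain over the planned test.

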## Results

Recruitment will be conducted from April 1 to May 31, 2025. The 12-week intervention period will run from June 1 to August 31, 2025. Final follow-up assessments will be completed by September 15, 2025. Data analysis is scheduled from October 1 to December 31, 2025. Manuscript drafting and submission are planned for March 2026.

## Discussion

### Anticipated Findings

It is plausible that both an STR program and a face-to-face physiotherapy program have positive effects on the primary and secondary outcomes of the study. This hypothesis is based on evidence from systematic reviews and meta-analyses that supports how exercise-based interventions generate benefits in muscle strength, balance, cardiorespiratory fitness, quality of life, and the number of daily steps in older people [35,38,70,71].

### Strengths and Limitations of This Study

We expect the STR program to offer results equal to or superior to those of the face-to-face physical exercise intervention, as this type of intervention has been described as an effective strategy to overcome the commonly reported barriers to access and adherence to physical exercise [24,27,29,30]. In addition, it would be of great interest to conduct a multicenter study in the future involving different cities and countries, thus confirming whether the results expected in this study could be replicated in other latitudes and social and geographical contexts. However, factors such as self-efficacy in using technological devices, motivation to practice physical activity [72], and the perception of loss of social support by not attending group sessions with people who share similar conditions [73] could interfere with the expected results of the telerehabilitation program in the intervened older adults. However, the personalized design of the program, with direct attention from a professional in charge of delivering the sessions, is expected to mitigate these limitations effectively.

While asynchronous telerehabilitation may represent a viable alternative that overcomes many of the barriers associated with in-person therapy, future clinical trials should directly compare synchronous and asynchronous modalities to determine their respective advantages and limitations. Furthermore, it is recommended that digital literacy measurement be considered, either as an inclusion criterion or as a covariate, to better understand its effect on treatment adherence and outcomes.

### Conclusions

Implementing STR programs could represent a viable and effective alternative to in-person physical therapy for older adults who are frail. This innovative approach would not only achieve comparable or superior improvements in strength, cardiorespiratory fitness, and other functional indicators but also facilitate access to rehabilitation by overcoming geographical and logistical barriers. Telerehabilitation would allow for the personalization and optimization of therapeutic resources, improving the quality of life and independence of a vulnerable population. These potential findings would have important implications for integrating remote strategies into routine practice and for fostering future research that expands their application in clinical settings.

## Appendix

Multimedia Appendix 1 SPIRIT checklist.

Multimedia Appendix 2 Peer review report by National Agency for Research and Development (ANID), FONDECYT, Ministry of Science Technology, Knowledge and Innovation (Chile).

## Abbreviations

CIAM: Centro Integral del Adulto Mayor (Comprehensive Center for the Older Adults)
CONSORT: Consolidated Standards of Reporting Trials
FPT: face-to-face physical therapy
HRmax: maximum heart rate
RPE: Rating of Perceived Exertion
SPIRIT: Standard Protocol Items: Recommendations for Interventional Trials
STR: synchronous telerehabilitation
